#### Intervention: Total Knee Replacement Platform

In stage 1, perioperative (typically 4 weeks before surgery) participants, upon receiving surgery date, will be provided with the TKR mobile app and a Garmin Vivosmart HR activity tracker at no cost. In stage 2, recovery (weeks 1-12 after surgery) participants will continue to use the TKR app and the activity tracker. Participants are expected to use the app daily and wear the activity tracker continuously (including while sleeping) for 16 weeks. Participants will continue to receive any prehabilitation and rehabilitation management as recommended by their surgeon, physiotherapist, or as provided by their hospital.

#### Control: Usual Care

Participants in the control group will receive the usual inpatient and outpatient prehabilitation and rehabilitation services as recommended by their surgeon, physiotherapist, or as provided by their hospital.

### Outcome Measures

#### Overview

Basic demographic data and a brief history of medical/health conditions will be taken at baseline. PO will be responsible for collecting responses from participants, either face-to-face at the clinic or received by post. OpenClinica (www.openclinica.com) will be used to store digital copies of responses from self-reported questionnaires, which include validated and trial specific questionnaires. The patient diaries and audit questions for health care providers will inform the economic outcomes for this study. Patient diaries will be documented online using SurveyGizmo (www.surveygizmo.com).

Interviews will be conducted with a selected number of patients, their carers, and clinicians in order to capture outcomes related to the TKR platform technology with regard to service delivery satisfaction and usability. Table 1 summarizes the outcome measures, the data collection tools and procedures, and the time points. The remainder of this section details the various outcome measures.

**Table 1 table1:** Outcome measures, data collection tools and procedures, and timeline.

Outcome		Measurement tool/procedure/ data collection	Time points (weeks)			
			*Baseline*	*0*	*12*	*52*
**Patient self-report**						
	Knee	OKS^a^	x	x	x	x
	Quality of life	SF-36^b^	x	x	x	x
	Depression, anxiety, stress	DASS21^c^	x	x	x	x
	Clinical satisfaction	Trial specific questionnaire			x	
	Service delivery satisfaction	Trial specific questionnaire		x	x	
	Technical satisfaction	Trial specific questionnaire			x	
	Self-motivation	SMI^d^		x		
	Self-determination	SDQ^e^		x		
	Self-efficacy	SES^f^	x	x	x	x
	Economic	Patient diary			x	
**By clinicians or project officer**						
	ROM^g^	Goniometer	x	x	x^h^	x
**Structured interviews**						
	Service satisfaction (patients, carers, clinicians)				x	
	Technical/usability (patients, carers, clinicians)				x	
**Audit**						
	Health care provider audit	Trial specific questionnaire			x	

^a^OKS: Oxford Knee Score.

^b^SF-36: Short-Form Health Survey.

^c^DASS21: Depression, Anxiety, and Stress Scale.

^d^SMI: Self-Motivation Inventory.

^e^SDQ: Self-Determination Questionnaire.

^f^SES: Self-Efficacy Scale.

^g^ROM: range of motion.

^h^At 6 weeks.

#### Primary Outcome

The primary outcome measure is self-reported knee pain and function as measured by the Oxford Knee Score (OKS) [23]. The OKS is 12-item questionnaire with 5 items for assessing pain and 7 for assessing function, each with 5 categories of response. Each item is scored from 1 to 5, from least to most difficulty or severity. A single combined score ranges from 12 (ie, least difficult) to 60 (ie, most difficult), and a lower score indicates a better outcome. The OKS has been developed and validated to specifically assess function and pain after TKR and is widely used by clinicians.

#### Secondary Outcomes

The secondary outcomes include:

Quality of life (RAND 36 Item Short-Form Health Survey [SF-36]): SF-36 is a 36-item questionnaire that will be used for constructing summary scores of physical and mental components [24]. The questionnaire assesses 8 domains of wellness through subscales including body pain, physical function, general health, mental health, social functioning, and emotional role. The SF-36 is a popular instrument in the knee domain to measure generic quality of life [25].Knee range of motion (ROM): A long-arm goniometer will be used for measuring the knee ROM (flexion and extension) [26]. The goniometer axis will be positioned over the lateral knee joint area and the arms will be aligned with the lateral malleolus using the greater trochanter. The active knee flexion will be measured in the sitting position and the active knee extension will be measured in the long sitting or supine position. ROM as part of week 12 will be collected during the patients’ follow-up clinical visit, typically 6 weeks following surgery.The Depression, Anxiety and Stress Scale (DASS21) will be used to measure mental well-being. This is a 21-item questionnaire using a 4-point Likert scale with 7 items per condition (depression, anxiety, stress) [27]. Each item has equal weighting (0 to 3) and a higher score indicates greater symptoms. While SF-36 covers general mental health (psychological distress and psychological well-being), DASS21 is specifically designed to measure negative emotional states and severity of feelings related to depression, anxiety, and stress and has proven to be sensitive to patients’ response to treatment.Satisfaction with knee surgery and service delivery (prehabilitation, rehabilitation) and the use of technology (eg, app and wearable) will be measured with questionnaires developed by the Commonwealth Scientific and Industrial Research Organization (CSIRO) using a 5-point Likert scale. The questionnaires are designed to capture surgical results, surgical recommendations, interaction with clinicians, empowerment experience, observability, and overall satisfaction with the service delivery. The technical satisfaction questionnaire will capture complexity, compatibility factors, and experience with the app and the wearable.Self-motivation will be captured using a validated 40-item scale [28] called the Self-Motivation Inventory (SMI). It has been used previously to assess rehabilitation outcomes for anterior cruciate ligament reconstruction [29]. The scale captures 10 areas of self-motivation and could be a critical predictor of adherence to a rehabilitation program. Therefore, we will be capturing this to control for any confounding effects that this may have on the experimental conditions.Self-determination will be captured using a 4-item questionnaire in order to assess whether the intervention group has higher levels of autonomous and/or intrinsic motivation after the presurgery phase (ie, week 0). In line with methods of Sheldon and Kasser [30], participants will be asked to rate 4 reasons for pursuing the goal of successful rehabilitation according to how much each describes their reason for having this goal. These reasons cover the proposed spectrum of possible motivations from external to introjected to autonomous to intrinsic, all derived from self-determination theory. All responses are rated from 1 (not at all because of this reason) to 9 (completely because of this reason).Self-efficacy to perform rehabilitation activities is a critical predictor of rehabilitation success. It describes a person’s confidence in their ability to perform certain behavior in the face of challenges. In order to capture changes in self-efficacy, we will be using an adapted version of a physical activity Self-Efficacy Scale (SES) [31] designed to ask these questions around rehabilitation physiotherapy exercises rather than general exercise intention. This is a 5-item questionnaire using a 4-point Likert scale.

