## Methods

### Overview and Aims

Data will be collected as part of a 13-month (for each participant), multisite unblinded RCT where participants are assigned to 1 of 2 study groups (1:1 allocation ratio). Both groups will undergo TKR surgery and be offered usual care and guidance from their surgeon and nominated health care team. In addition, the intervention group will receive the TKR app and a Garmin Vivosmart HR activity tracker. Patient participants will be scheduled for TKR surgery and managed through a project officer (PO), typically a member of the clinical team. Participants in the intervention group will be provided with instruction from the site PO in regard to using the technology. The aims of the study are as follows:

To determine the efficacy of the TKR platform in delivering clinical and behavioral outcomes by specifically evaluating group differencesTo understand the impact of the TKR platform components and level of satisfaction with surgery and the care deliveryTo evaluate economic benefits

The study includes an active intervention period commencing when the patient is scheduled for surgery (approximately 4 weeks before surgery) and ending when the patient is 12 weeks postoperative. This is followed by a 40-week free-living period, finishing 1 year after surgery. Paper-based questionnaires will be completed by participants and the PO will be responsible for collecting responses from participants at 4 time points as illustrated in Figure 2.

All access to data will be controlled by authentication and authorization protocols designed to ensure the data is protected and only accessible by authorized persons. All information identifying the participants will be de-identified by a member of research team.

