### Sample Size

The sample size is calculated based on the primary outcome (ie, OKS), by considering 80% power (*P*=.05) with a 15% difference in the control group and the intervention group. The standard deviation within each group in the TKR trials can vary based on factors such as number of trial sites (eg, single-center vs multicenter) and heath care cover (eg, public patients vs private patients). Furthermore, in a repeated measure scenario or when considering multiple assessments within a trial (eg, baseline, prehabilitation, 12 weeks rehabilitation, 12 months free living), the correlation among repeated measures needs to be considered as well. Based on these factors the sample size is presented in Table 2 for a variety of scenarios. A low subject variation can be expected with participants when considering only 1 trial site or 1 type of health care cover (eg, public), and a high variation can be expected when participants are mixed. A high correlation in repeated measures can be expected for patients with big differences in the outcome measure within the assessment points.

**Table 2 table2:** Estimated sample size (with 20% loss) based on standard deviation (SD) within groups and correlation among baseline and 3 repeated measures [80% power, *P*=.05, 15% difference].

SD within group/ correlation repeated measure	Low repeated correlation (SD 0.2)	Mid repeated correlation (SD 0.5)	High repeated correlation (SD 0.8)
Low subject variation (SD 0.2)	31	46	60
Mid subject variation (SD 0.5)	170	262	360
High subject variation (SD 0.8)	432	674	914

We estimate that a total of 262 patient participants would be sufficient for this study; however, we expect a maximum of 320 participants from the 5 trial sites based on their rate of TKR surgeries during the trial timeline. A minimum sample size of 100 is suggested for using OKS as the primary outcome measure [33]. Based on the literature [1,7,34], 80% power (*P*=.05) with a 15% difference in the control group and the intervention group has been reported for primary outcome measure.

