### Statistical Analysis

Statistical data analysis will be performed using an intention-to-treat approach. Mixed model analysis will be used for continuous variables (primary and secondary outcomes) measured at week 0, week 12, and week 52 for those receiving the TKR platform compared with usual care by time effects. Fixed effects will be included for the intervention, the time points, and the interaction between the 2 variables. These models will also account for relevant covariates such as baseline (4 weeks before surgery) measures, participant sex, baseline levels of motivation, etc. These covariates will be entered as fixed effects. Due to potential confounding effects between different hospitals, these will be also assessed in the mixed model as random effects. Sensitivity analysis will be used to assess the impact of these covariates before the final model is constructed. Other outcome measures of app usage, self-management (eg, physical activity), and compliance with the program (eg, physiotherapy exercise) will be analyzed using logistic or conditional logistic regression to adjust the comparisons for other variables for categorical or ordinal variables and multiple regression for continuous variables. All statistical analysis will be done using Excel (Microsoft Corp), R (R Foundation), or SPSS (IBM Corp).

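### Self-determination has a stated between-arm aim at week 0 but no baseline measurement, so that comparison is valid but less precise than four extra baseline items would make it

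*Protocol article*

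**What the plan says.** In the Protocol article, Secondary Outcomes gives the self-determination questionnaire (SDQ) a between-arm purpose: to "assess whether the intervention group has higher levels of autonomous and/or intrinsic motivation after the presurgery phase (ie, week 0". Table 1, under patient self-report, marks "Self-determination" at week 0 only; its baseline, week-12 and week-52 cells are empty. The text and the table agree on the timing.

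Overview and Aims describes the active intervention as "commencing when the patient is scheduled for surgery (approximately 4 weeks before surgery) and ending when the patient is 12 weeks postoperative". The single SDQ value is therefore taken after about 4 weeks of exposure.

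Statistical Analysis gives one model for continuous outcomes: "Mixed model analysis will be used for continuous variables (primary and secondary outcomes) measured at week 0, week 12, and week 52". Its fixed effects are intervention, time and their interaction, with hospital as a random effect. On covariates it says: "These models will also account for relevant covariates such as baseline (4 weeks before surgery) measures, participant sex, baseline levels of motivation, etc".

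The Oxford Knee Score (OKS), SF-36, DASS21, Self-Efficacy Scale and range of motion all have a baseline measurement in Table 1.

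**The concern.** The SDQ is the listed measure whose stated aim is to test whether the pre-surgery phase shifts the type of motivation. The section on the platform technology says the app's motivational content was built on self-determination theory, and the Discussion links rehabilitation compliance to motivation or self-determination. If the week-0 comparison shows no difference, the team will want to know whether the content had no effect or the test was too imprecise to see one.

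Patients probably differ in motivation before they receive anything. A baseline value would remove the part of that variation that persists to week 0. Without it, the plan's baseline adjustment cannot use the covariate likely to help most for this outcome. The collection schedule is fixed in the protocol, and no later analysis plan can recover a baseline that was never collected.

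**Working it through.** **1. The plan's own figure.** The sample size rests on the OKS, "by considering 80% power (*P*=.05) with a 15% difference in the control group and the intervention group". Table 2 gives 262 for SD 0.5 and correlation 0.5, with 20% loss. Take the mean of 4 equally correlated measures and a two-sided 5% test (the sidedness is not stated, but two-sided reproduces the figure):

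- Variance of the mean: 0.5² × (1 + 3 × 0.5)/4 = 0.15625.
- n per arm: 2 × (1.960 + 0.842)² × 0.15625/0.15² = 109.0.
- Total: 218.0. With the loss, 218.0 × 1.2 = 261.6, which matches 262.

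This figure concerns the OKS and is not affected by the present point. The protocol gives no power or sample size for the SDQ.

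**2. Inputs for an illustration on the SDQ.**

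- Difference d = 0.15/0.5 = 0.3 SD. This is borrowed from the OKS scenario; nothing in the protocol ties it to the SDQ.
- Patients analysed, N: 218 (262 before the loss allowance), 262 (no loss by week 0) and 320 (the expected maximum, no loss).
- Correlation ρ between baseline and week-0 SDQ: not given in the documents, so assumed from 0.2 to 0.7.

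**3. Formulas.** With 1:1 allocation, unadjusted week-0 power ≈ Φ(d√N/2 − 1.960). Adjusting for baseline multiplies the residual variance by 1 − ρ², so power ≈ Φ(d√N/(2√(1 − ρ²)) − 1.960).

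Example with N = 262:

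- Unadjusted: 0.3 × 16.186/2 = 2.428, and Φ(0.468) = 68.0%.
- Adjusted at ρ = 0.5: 2.428/0.866 = 2.804, and Φ(0.844) = 80.1%.

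**4. Results: power for a 0.3 SD difference.**

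| N analysed | Week 0 only | ρ = 0.2 | ρ = 0.3 | ρ = 0.5 | ρ = 0.7 |
|---|---|---|---|---|---|
| 218 | 60.1% | 61.8% | 64.1% | 72.5% | 87.3% |
| 262 | 68.0% | 69.8% | 72.1% | 80.1% | 92.5% |
| 320 | 76.5% | 78.2% | 80.3% | 87.3% | 96.4% |

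The difference detectable with 80% power, 2 × (1.960 + 0.842)/√N in SD units, is 0.379, 0.346 and 0.313 for the three sample sizes. Adjusted at ρ = 0.5, it falls to 0.329, 0.300 and 0.271.

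**5. A comparison that does not depend on d or N.** Where the adjusted analysis has 80% power, the unadjusted one has Φ(2.802 × √(1 − ρ²) − 1.960). This is 78% at ρ = 0.2, 76% at 0.3, 68% at 0.5 and 52% at 0.7.

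**The case against.** The strongest reply is that nothing is invalid. Comparing randomised arms at week 0 is a legitimate design, and the stated aim asks whether the intervention group is higher at that time, not whether levels changed. Self-efficacy, which the protocol wants in order to capture change, is scheduled at all four times. This stands: a reader might infer that the comparison is biased because it is made after exposure, but randomisation protects it.

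A reader might also infer that the protocol promises an SDQ baseline and that its model therefore cannot be fitted. The documents do not support that. The covariate list is illustrative, and the mixed model is described for variables measured at weeks 0, 12 and 52, which the SDQ is not. The time and interaction terms do not apply to an outcome measured once, but a week-0 model with arm, hospital, sex and other baseline measures, such as self-efficacy and DASS21, can be fitted. Setting out such a model is commonly left to a statistical analysis plan.

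Those other covariates also mean that the unadjusted comparison is not the planned one. They may already absorb some between-patient variation, so the gains in the table are upper bounds.

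Finally, the 60% figure should not be read as the trial's power for this outcome. It borrows the OKS effect and applies a loss allowance from a calculation that runs to week 52, whereas the SDQ is taken about 4 weeks after entry. With no loss by week 0, the figure is 68% to 77%.

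What survives is narrower. The best available precision covariate is not collected, and the other motivation scale cannot replace it: Table 1 also takes the Self-Motivation Inventory only at week 0, after exposure.

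**Conclusion.** The point holds as an inexpensive improvement in precision, not as an error of validity. Leaving out the SDQ baseline inflates the variance of the week-0 comparison by up to 1/(1 − ρ²): 1.04 at ρ = 0.2, 1.33 at 0.5 and 1.96 at 0.7. With 262 analysed and a 0.3 SD difference, the possible gain in power runs from under 2 points at ρ = 0.2 to about 12 at 0.5 and 24 at 0.7. The effect size and the correlation are both assumptions, so the documents cannot show that the loss is large. The primary outcome and its sample size are untouched.

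**What to change.** - Add the four-item SDQ to the questionnaires already given at baseline, completed before the allocation is known and before the app is issued. Mark the baseline cell in Table 1.
- State that self-determination is analysed at week 0 by a single-time-point model with arm, baseline self-determination and hospital, and that the time and interaction terms do not apply to it.
- Keep patients enrolled before the change in the analysis, using a prespecified missing-baseline method. The Results section says one site started in October 2016 and the others were expected early in 2017, so the number affected depends on when the change is made.

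The cost is a minor amendment and about a minute of patient time, with no new procedure or extra staff. If the sponsor prefers not to amend data collection, one sentence saying that the SDQ is compared at week 0 without its own baseline would make the plan clear, but it would not recover the precision.

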
#### Technical and Usage Outcomes

Usage logs for the TKR platform (app, activity tracker, and Web portal) will be gathered and analyzed to help understand technology uptake and feature usage by patients and clinicians. Correlations and dependencies between usage and outcomes will be evaluated. Self-reported compliance with physiotherapy programs, content access, activity tracker data, and goal achievements collected from the app will also be analyzed.

#### Health Economic Outcomes

The economic evaluation will assess the costs and benefits accruing to both patients and service providers. It will also consider broader economic impact such as impact on carers’ time, ability to work, and other health system costs (eg, visits to general practitioners).

For service providers, we will estimate the delivery costs of group or one-on-one classes that deliver physiotherapy intended for self-guided physiotherapy including staff time, space, and equipment costs. Each trial site will complete a health care provider audit form for this purpose. Further to this, we will note the time taken to review patient data through the TKR clinical Web portal, time taken on patient phone calls, etc.

For patients and their carers, we focus on the direct and indirect costs, such as impact on work or spare time, various services patients receive from the community, visits they make to see their health care professional, visits related to any nonclinical services, and an estimate of out-of-pocket expense. In most cases patients will not be asked to estimate monetary costs as these are highly variable and often subsidized (eg, by government or health insurers). The research team will assign generic costs to each activity or impact for the analysis. This approach allows the costs and benefits to other stakeholders such as government and health insurers to also be compared across the 2 treatment groups.

#### Interview Participants

Using a maximum variation sampling [32] technique, intervention group patients (n=20), carers (n=10), and surgeons/physiotherapists (n=10) will be recruited by the site POs with guidance from the CTC for interview. Previous experience suggests that theoretical saturation will be reached with these numbers and a pool of diverse participants will be identified. Patient diversity will focus on gender, age (over 18 years only), TKR experience, education level, and private versus public health care. Carer sampling will target spouses, children, and friends of patients, with a balance of gender and age. All participating clinicians will be invited for interview by a researcher.

Interviews will be semistructured. Interviews will be audiorecorded and transcribed and analyzed using NVivo (QSR International) software. Interviews with patients and carers will focus on technology acceptance, their experience with the app, and what features they liked and disliked. Interviews with surgeons and physiotherapists will focus on features of the clinical Web portal and the usefulness of the portal for monitoring patients postoperatively.

Inclusion criteria for carers include the following: be the person who is nominated as the primary carer after hospital discharge of a patient participating in the TKR study from the intervention group (ie, using the app and activity tracker), be sufficiently healthy to not be adversely affected by the participation in the interview or study, and have the willingness to participate in the study and be interviewed. Clinicians must have provided care to at least 1 patient participant in the TKR study to take part in the interview.

Carers and clinicians participating in an interview will be sent the information sheet and consent form by email or post, separate from the ones used for patients. Paper-based consent will be obtained in face-to-face interviews, and verbal consent will be obtained for telephone interviews.

Estimated times for patient and carer interviews are 30 to 45 minutes, and estimated time for clinicians is 45 to 60 minutes.

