## Discussion

Variations in the provision of care by health care providers, rising health care costs, and the increased uptake of TKR surgery have recently contributed to the need to ensure that TKR is effective, efficient, and safe as this can have a significant impact on patient satisfaction, medical costs, and access to health care service [35,36]. Rehabilitation programs after TKR surgery are designed to assist in recovery, restoring functional independence through physiotherapy programs and other interventions supporting the process. The programs have been popular in Western countries with both inpatient and outpatient settings.

It is evident that rehabilitation programs are costly and mostly accessed by private health care patients. Patients generally have the option of inpatient or outpatient rehabilitation after TKR. Inpatient rehabilitation clinics are only available in large metropolitan areas and because of the cost only an option for private insured patients [37]. Outpatient rehabilitation usually commences immediately after hospital discharge, which provides supervised (ie, one-on-one or group) exercises to the patients by a physiotherapist and is completed within 6 to 8 weeks after TKR surgery [7,38]. Outpatient rehabilitation has a large component of self-managed exercise at home. Compliance with in-home exercise is a recognized challenge in physiotherapy [39]. Compliance with rehabilitation physiotherapy after TKR is dependent on motivation or self-determination [18].

Our study will test whether a digital orthopedic rehabilitation platform comprising a smartphone-based program with a wearable activity tracking device and a clinical Web portal where clinicians monitor patients can assist TKR patients and their carers in the TKR journey. The proposed platform will provide flexibility, particularly in rural, remote, or busy lifestyles, and has the potential to achieve the same clinical outcomes as normal business as usual care.

Potential barriers to participant adaptation of the intervention may include a lack of technology/eHealth literacy for the targeted age group, contributing to the unwillingness to continue using the app and the wearable activity tracker. The trial is a research project rather than a new health service. It requires clinicians and POs at trial sites to help participants follow the protocol while integrating the intervention into their usual care model.

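### Interview patients are sampled on five characteristics but not on app or tracker use, so low users and those who stopped may be under-represented in the acceptance findings

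*Protocol article*

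**What the plan says.** Under Interview Participants, the protocol article states that "intervention group patients (n=20), carers (n=10), and surgeons/physiotherapists (n=10) will be recruited by the site POs with guidance from the CTC for interview", using a maximum variation technique. For patients it then gives the dimensions: "Patient diversity will focus on gender, age (over 18 years only), TKR experience, education level, and private versus public health care". On content it says: "Interviews with patients and carers will focus on technology acceptance, their experience with the app, and what features they liked and disliked". Table 1 places the interviews at week 12.

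Three other places bear on this:

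- Overview and Aims describes patients as "managed through a project officer (PO), typically a member of the clinical team" and adds: "Participants in the intervention group will be provided with instruction from the site PO in regard to using the technology".
- Technical and Usage Outcomes says that usage logs for the app, tracker and portal "will be gathered and analyzed to help understand technology uptake and feature usage by patients and clinicians".
- The Discussion names low technology literacy in this age group as a potential barrier, "contributing to the unwillingness to continue using the app and the wearable activity tracker".

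**The concern.** Maximum variation sampling is meant to spread a small sample over the attributes that could shape the answers. Here the subject is acceptance of the app and tracker, and the most direct observable sign of acceptance is whether a patient went on using them. That attribute is not listed, although the article foresees that some patients will not want to continue and already collects the data that would identify them.

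The recruitment route adds to this. The site officers who recruit interviewees have taught these patients to use the technology and are usually part of the clinical team. They may know who is engaged, and engaged patients are often the easier ones to approach.

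At stake is the qualitative account of acceptance and of why patients stopped. That account serves the trial's second aim, on the impact of the platform components and satisfaction.

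**Working it through.** **Step 1: set the sections side by side.**

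- Purpose of the patient interviews: acceptance, experience with the app, likes and dislikes (Interview Participants).
- Sampling dimensions: gender, age, experience of knee replacement, education, private or public care (same section). Level of use and having stopped are absent.
- Stopping is foreseen (Discussion), and a measure of use exists for every intervention patient (Technical and Usage Outcomes).
- Recruiters: site officers with coordinator guidance (Interview Participants), who also give the technology instruction (Overview and Aims).
- For clinicians, the same section has a researcher issue the invitation, so a route that does not run through the site officer is already in the plan.

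Twenty patients can be balanced on all five listed dimensions and include nobody who stopped. Nothing in the text prevents this.

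**Step 2: illustrate the size.** The plan gives no figure to reproduce; the number 20 rests on expected saturation, not on a formula. The illustration needs two inputs that the document does not supply, so both are assumptions and are varied:

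- s = share of intervention patients who stopped (10%, 20%, 30%);
- w = their chance of being picked relative to a continuing user (1, 0.5, 0.25).

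The chance that any one interviewee is someone who stopped is p = s·w / (s·w + 1 − s). The expected number among 20 is 20p, and the chance of none is (1 − p)^20. For s = 20% and w = 0.25: p = 0.05 / 0.85 = 0.0588, expected number 1.18, chance of none 0.9412^20 = 0.297.

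| s | w | p | Expected of 20 | Chance of none | Chance of two or fewer |
|---|---|---|---|---|---|
| 10% | 1 | 0.100 | 2.0 | 12.2% | 67.7% |
| 10% | 0.5 | 0.053 | 1.05 | 33.9% | 91.5% |
| 10% | 0.25 | 0.027 | 0.54 | 57.8% | 98.4% |
| 20% | 1 | 0.200 | 4.0 | 1.2% | 20.6% |
| 20% | 0.5 | 0.111 | 2.22 | 9.5% | 61.3% |
| 20% | 0.25 | 0.059 | 1.18 | 29.7% | 89.0% |
| 30% | 1 | 0.300 | 6.0 | 0.1% | 3.5% |
| 30% | 0.5 | 0.176 | 3.53 | 2.1% | 28.8% |
| 30% | 0.25 | 0.097 | 1.94 | 13.1% | 69.5% |

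This treats the 20 as independent draws. With 320 enrolled 1:1 there would be 160 intervention patients. Drawing without replacement from 160 with 16 who stopped gives 10.5% for the first row instead of 12.2%, so the simplification matters little. Purposive selection is not a random draw, so the table shows only how strongly the result depends on the selection.

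**Step 3: read the result.** If selection is unrelated to use and stopping is not rare, some who stopped will probably be interviewed. If it is related to use, there may be one or none. The plan does not fix which of these applies.

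**The case against.** The strongest reply is that nothing here is misstated. Maximum variation is a recognised method, the numbers and dimensions are given, the wording on diversity is not strictly exclusive, and recruitment has guidance from the trial coordinator, so there is central input. The dimensions are not merely demographic either: surgical experience and type of care are included. The document does not say that site officers know who is engaged or would favour such patients. On this view, a different list of dimensions is a matter of preference.

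Much of this stands. It limits the point to a risk in a secondary, qualitative component. It does not supply the missing dimension: the list is a stated choice, and the attribute closest to the interview topic is not on it.

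A reader might also go further in two ways that the document does not support:

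- **That the age dimension does no work because of the over-18 qualifier.** Patients are aged 50 to 80 under Selection Criteria, so age can still vary the sample. Only the adult floor is redundant for patients.
- **That the trial could not explain non-use or a null primary result.** The logs record use, and their relation to outcomes is to be evaluated (Technical and Usage Outcomes). Usage and compliance are to be modelled (Statistical Analysis). A week-12 technical satisfaction questionnaire, which the article does not restrict to interviewees, covers complexity, compatibility and experience with the app and wearable. What could be thin is the detail on why patients stopped.

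**Conclusion.** The point holds as a cheap improvement. As written, the interview sample may under-represent low users and those who stopped, so what the interviews report on acceptance and reasons for stopping can look more favourable than it is. That direction is plausible, not shown: it rests on the assumption that engaged patients are more likely to be approached or to agree.

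The size is unknown. Across assumed stopping shares of 10% to 30%, the chance of interviewing nobody who stopped is 0.1% to 12.2% under equal selection and 13.1% to 57.8% if those who stopped are a quarter as likely to be picked. The Oxford Knee Score comparison, the usage logs and the technical satisfaction questionnaire are unaffected.

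**What to change.** In Interview Participants:

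1. Add level of use, taken from the usage logs, as a maximum variation dimension with three classes (high, low, stopped). Define the classes before any candidate list is drawn.
2. State a minimum number among the 20 who are low users or have stopped. The number is a judgement for the team, but it should be fixed in advance.
3. Have the coordinator or the research team draw the candidate list from the logs, with the site officer only making contact.
4. Record invitations and refusals by class of use, so that readers can see whether low users were approached and declined.

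The number of interviews stays at 20 and no new data are collected. The costs are a query of the logs as patients near week 12, more contact attempts for low users, and slightly less room for the other five dimensions.
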